### Variables and measurements

The selection of variables was guided by the ecological model, shown in Fig. 1, which considers the influence of multiple levels of health care as potential determinants of a patient’s behaviour [9, 50]. Variables are measured using established instruments, investigator-developed measures specific for this study or collected from medical records. A detailed description of the instruments and operational definitions used are summarized in Additional file 1: Tables S1 and S2.

#### Behavioural factors

The implementation phase of medication adherence (taking and timing dimensions, drug holidays and dose reduction) [51] to immunosuppressive drugs is measured using three methods: a validated self-report (Basel Assessment of Adherence with Immunosuppressive Medication Scale - BAASIS) [28, 43], blood assay [52], and collateral reports by health care workers [53]. In addition to the evaluation provided by each individual method, a composite adherence score is calculated. Overall non-adherence to immunosuppressants will be defined by a positive finding on any one of the three assessment methods [27, 29]. For blood assay of immunosuppressants, the actual level and the levels in the two previous assays are being used [29, 46], as described in Additional file 1: Table S1.

The current physical activity level [54, 55], smoking status [18, 56], alcohol use [18, 57], and appointment keeping [18] are assessed by using investigator-developed questions based on previous transplant research. These questions are presented in Additional file 1: Table S1.

#### Multilevel correlates of non-adherence to immunosuppressive medication

##### Patient level

Demographic (age, sex, race, education, employment status, marital status, family income), disease related (aetiology of kidney disease, treatment modality prior to transplant, preemptive transplant, time on dialysis, donor type, post-transplant time, comorbidity, height, weight), and therapy related data (drugs of immunosuppressive schema, number of immunosuppressive medications, daily number of doses of immunosuppressants) are collected through structured interview and review of charts [20, 26, 58–61]. The following post-transplantation clinical data is collected from medical charts: number of treated acute rejection episodes, creatinine level, estimated glomerular filtration rate, and re-hospitalizations [52, 61–64] (Additional file 1: Table S2).

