**Fig. 2 Fig2:**
[figure not shown]
Location of centres participating in the study. Transplant activity is indicated in colour, as follows: Red, high activity (> 150 kidney KTs/year); green, moderate activity (50 to 150 KTs/year); blue, low activity (< 50 KTs/year)

KT patients are randomly selected using a computer-generated list (Blockrand package for R language) and screened according to the following inclusion criteria: recipient of single and first KT; age > 18 years; > 1-year post-transplant; and ability to understand the objectives of the study. Patients are excluded if the immunosuppressive regimen is only based on drugs for which the blood monitoring is not available or not covered by Brazil’s health care system, e.g. mycophenolates without calcineurin or proliferation signal inhibitors. Patients randomly selected and meeting our inclusion criteria are invited to participate during their routine medical consultation visits, and those providing written informed consent are enrolled.

Using the OpenEpi stats program, the sample size was calculated for studies of population prevalence. Population size was defined based on data from the 2012 Brazilian Registry of Transplant (RBT 2012) available through the Brazilian Association of Transplantation [49]. Of the 57,815 patients who received a KT in Brazil from 2000 to 2012, we only considered the 31,241 patients registered to be under follow up in RBT 2012 as eligible for our calculation. Based on a non-adherence prevalence rate of 50%, the 95% confidence interval with a 5% sample error, and a design effect of 3.0, a sample size of 1139 patients was calculated and, considering the multi-stage design of the study, divided into approximately 283 patients in each stratum.

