The use of a consistent methodology of non-adherence to medication measurements will provide an accurate prevalence and allow us to conduct reliable comparisons between centres, regions, and clinical practice patterns. Our sampling methodology tried to avoid selection bias of patients, given that the centres were selected by convenience. Recruiting centres from all regions, and then including different patterns of clinical practice, administration and transplant activity, and a randomized selection of patients, will increase the reliability of the study findings to Brazil and to other countries with similar health systems. The multilevel analysis of factors associated with non-adherence, including at the level of the patient, healthcare provider, health care organization, health care system and policies, will enable us to capture a wide range of factors correlated to non-adherence. Furthermore, we believe that the identification of the clinical practice patterns positively associated with adherence might be the most valuable potential contribution of this study, and such practices can be promptly adopted in KT care. This information, for the first time involving a large sample of KT patients, will provide an accurate view of the current state of non-adherence after KT, and identify targets for further interventions. Data collection using the RedCap system promotes a constant and ongoing quality surveillance of included data. The RedCap system provides a useful tool for collecting data across multiple centres and for problem solving, at a distance, which is essential considering that our study covers a territory of 328,804 mi^2^ and 200 million inhabitants. As another relevant point, we will provide feedback to each centre regarding their patients’ adherence behaviours, which the centres can use to improve their clinical practice.

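### The drug regimen decides what the blood limb of non-adherence can measure and is also a listed correlate of non-adherence, and a sensitivity-only rationale does not support an accurate prevalence

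*Protocol article*

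**What the plan says.** All references are to the protocol article.

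- **Outcome (Behavioural factors).** Three methods are used: the BAASIS self-report, blood assay and collateral report by staff. "Overall non-adherence to immunosuppressants will be defined by a positive finding on any one of the three assessment methods". On the blood limb: "For blood assay of immunosuppressants, the actual level and the levels in the two previous assays are being used". The detailed rule is referred to Table S1 of the additional file, which is not shown. Results by single method are also planned: "In addition to the evaluation provided by each individual method, a composite adherence score is calculated".
- **Eligibility (Sampling design and setting).** "Patients are excluded if the immunosuppressive regimen is only based on drugs for which the blood monitoring is not available", or not covered by the health system. The example given is "mycophenolates without calcineurin or proliferation signal inhibitors". A patient on a monitored drug plus an unmonitored one is therefore eligible and can be assayed only on the former.
- **Correlates (Patient level).** Under the heading for correlates of medication non-adherence: "therapy related data (drugs of immunosuppressive schema, number of immunosuppressive medications, daily number of doses of immunosuppressants) are collected".
- **Analysis (Statistical analysis plan, Aim 2).** The binary non-adherence indicator is related to the multilevel correlates by GEE with a Poisson distribution and log link, giving prevalence ratios. Relevance is judged by effect size, precision and p-value. The text does not say which non-adherence indicator is meant.
- **Claim (Discussion).** "The use of a consistent methodology of non-adherence to medication measurements will provide an accurate prevalence". The Background and the limitations paragraph support combining methods by sensitivity, and neither gives a specificity.

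**The concern.** The regimen enters the analysis twice. It determines which drugs the blood limb can test, and it is a candidate explanation for the result. If fully adherent patients on one regimen are flagged by the blood limb more often than those on another, the any-positive rule carries that difference into the composite. A prevalence ratio for the drug, or for the number of drugs, would then reflect how the assay rule behaves as well as how patients behave. Nothing in the article separates the two.

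The second issue is what the prevalence figure can bear. An any-positive rule raises sensitivity and lowers specificity. A rationale that speaks only to the first does not show that the resulting prevalence is accurate.

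At stake are the reading of the regimen correlates in Aim 2 and the strength of the Aim 1 prevalence claim.

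**Working it through.** **The plan's own figure.** The only computed figure is the sample size. With N = 31,241, p = 0.5, d = 0.05, z = 1.96 and design effect 3:

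n = 3 × 31,241 × 0.25 / [(0.05²/1.96²) × 31,240 + 0.25] = 23,430.75 / 20.58 = 1138.5, rounded up to 1139.

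It reproduces and does not bear on this point. The article gives no sensitivity, specificity or positivity rate for any method or drug, so everything below uses assumed values and independent methods.

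**Step 1: regimen artefact.** Take two regimens with the same true adherence. Let q be the proportion positive on self-report or collateral report, and b the proportion positive on the blood limb. Then

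composite = 1 − (1 − q)(1 − b).

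| q | b, regimen A v B | composite A v B | ratio |
|---|---|---|---|
| 0.30 | 0.10 v 0.20 | 0.37 v 0.44 | 1.19 |
| 0.30 | 0.10 v 0.30 | 0.37 v 0.51 | 1.38 |
| 0.30 | 0.20 v 0.40 | 0.44 v 0.58 | 1.32 |
| 0.40 | 0.10 v 0.20 | 0.46 v 0.52 | 1.13 |
| 0.40 | 0.10 v 0.30 | 0.46 v 0.58 | 1.26 |
| 0.40 | 0.20 v 0.40 | 0.52 v 0.64 | 1.23 |
| 0.50 | 0.10 v 0.20 | 0.55 v 0.60 | 1.09 |
| 0.50 | 0.10 v 0.30 | 0.55 v 0.65 | 1.18 |
| 0.50 | 0.20 v 0.40 | 0.60 v 0.70 | 1.17 |
| any | equal | equal | 1.00 |

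The artefactual ratio runs from 1.09 to 1.38 when the blood limb differs, and is 1.00 when it does not.

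**Step 2: number of monitored drugs.** Suppose, as a further assumption, that any one out-of-range level flags the patient and that each level is falsely flagged 5% of the time, independently. One drug with three levels gives 1 − 0.95³ = 0.143. Two drugs with three levels each give 1 − 0.95⁶ = 0.265. With q = 0.40 the composite is 1 − 0.6 × 0.857 = 0.486 against 1 − 0.6 × 0.735 = 0.559, a ratio of 1.15. The article does not say how many patients, if any, take two monitored drugs.

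**Step 3: accuracy of the any-positive rule.** Under any dependence between methods, composite specificity cannot exceed that of the least specific limb. Under independence it is the product of the three: 0.95³ = 0.857, 0.90³ = 0.729, 0.80³ = 0.512. So 14%, 27% or 49% of adherent patients would be called non-adherent.

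Apparent prevalence = π × Se + (1 − π) × (1 − Sp), where π is the true prevalence and Se and Sp belong to the composite.

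- π = 0.35, per-method sensitivity 0.6: Se = 1 − 0.4³ = 0.936. Per-method specificity 0.95, 0.90 or 0.80 gives 42%, 50% or 65%, all above the truth.
- π = 0.50 (the planning value), per-method sensitivity 0.4 and specificity 0.95: Se = 1 − 0.6³ = 0.784, and 0.5 × 0.784 + 0.5 × 0.143 = 46%, below the truth.

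The net bias can therefore have either sign.

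**The case against.** The strongest objection is that the regimen artefact needs blood-limb false positives to differ by drug, and the rule that decides this is in a table that is not shown. That table may set drug-specific targets, or use a mean, a variability measure or a majority of the three levels. The article does not say that drugs differ in level variability. This stands: a reader might infer that a regimen association would be an artefact, and the documents do not support that. They support only the possibility. Drug-specific cut-offs could reduce the difference but would not by themselves make false-positive rates equal.

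A reader might also infer that the composite prevalence is biased upward or is an upper bound. Step 3 shows that it need not be, because the same rule recovers missed cases. Nor does it follow that other prevalence ratios are pulled toward 1; that would need error unrelated to the correlate.

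Parts of the issue are already handled. Single-method results are planned, regimens with no monitored drug are excluded, the Background admits that there is no gold standard and that prevalence varies with method, and the limitations disclaim causal inference. These points stand and narrow the concern. They do not commit Aim 2 to a regimen analysis without drug levels. Aim 2 does not name its indicator, but the composite is the only one labelled overall non-adherence and is the natural reading.

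Making BAASIS the headline would be a trade-off and not a correction. It gives up sensitivity, and because it covers taking and timing, more daily doses may mean more chances to miss one. The Discussion's phrase, finally, describes the measurement methodology in general and not expressly the composite. The composite is nevertheless part of that methodology.

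**Conclusion.** The overlap is in the text: the regimen determines what one limb of the outcome can test, and the drugs and their number are listed as correlates of that outcome. A regimen prevalence ratio on the composite may therefore be partly definitional. With assumed positivity rates and independent limbs the artefact is about 1.1 to 1.4. Its existence and direction are unproven, and it vanishes if blood-limb positivity is equal across regimens.

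The accuracy wording goes further than its support. The rationale cites sensitivity only, and the size and sign of any bias depend on both error rates, which the article does not give.

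This is a point about interpretation and wording with an inexpensive check. It is not a demonstrated bias or a numerical error.

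**What to change.** 1. Keep the composite. For the regimen variables (drugs, number of drugs, daily doses), also estimate prevalence ratios on an outcome without the blood limb: BAASIS alone, or BAASIS or collateral report.
2. State in advance that a regimen association seen only when the blood limb is included will be interpreted as possibly definitional.
3. Describe the composite prevalence as a sensitivity-maximising estimate, present it with the single-method prevalences already planned, and drop the description of it as accurate.

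The cost is one extra set of models on data already being collected, and a more cautious claim in the report. An outcome without the blood limb is less sensitive and has its own error, which is why it is proposed beside the composite and not in its place.

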##### Health care provider level (Micro level)

A patient’s trust in the transplant team and satisfaction with his/her relationship with health care providers are evaluated using a visual analogue scale (VAS) [65]. Social support provided to the medication taking is also assessed by two questions [18] (Additional file 1: Table S2).

##### Health care organization level (Meso level)

With regard to CIM, we include questions on patient-centred care, continuity and coordination of care, information and communication technology, organization, and continuous education provided [18, 66, 67]. Demographic characteristics [20, 67, 68] and satisfaction with operational access to the transplant centre are also collected [14, 69]. All data are collected through a self-report questionnaire completed by a nurse or physician nominated by the transplant centre manager (Additional file 1: Table S2).

##### Healthcare system and policy level (Macro level)

For KT patients, the Brazilian Public Health System offers outpatient follow-up, immunosuppressive drugs, laboratory exams, and hospitalizations. As the public system is sometimes inefficient in providing access to the required exams and to hospitalization, some individuals do choose to pay for a complimentary private health insurance. Self-reported financial burden is assessed by identifying the complimentary private health insurance status [20]. City and region specific data related to health care access, such as number of hospitals and the number of intensive care beds available, and relevant information about the transplant centre are retrieved from the 2012 RBT [49], as summarized in Additional file 1: Table S2.

### Recruitment/data collection

Recruitment and data collection are centrally managed by the coordinator centre, the Federal University of Juiz de Fora, Juiz de Fora. After obtaining approval of the project by the ethics research board (ERB) of the coordinating centre, all invited centres submitted the project to their local ERB. All data collection is performed using the Research Electronic Data Capture (RedCap) system. Local research coordinators receive a detailed step-by-step training guide, followed by a specific training session via phone or podcast. Backup support for data collection is continuously available through the ADHERE BRAZIL study via phone, e-mail, or Skype. Once the project is locally approved by ERB and the local research team has been trained, the access to RedCap system is provided through a unique identification and password. This allows the centre to update and visualize only its data. The RedCap system is a safe internet program, created by Vanderbilt University, designed exclusively for the capture and storage of data that can accessed remotely by trained individuals. RedCap allows data to be collected, organized, and stored in an integrated manner, making the process of data analysis less time-consuming and feasible across multiple centres. Furthermore, users can access their database at any time to complete or update their data over the collecting time (http://www.project-redcap.org/).

#### Patient data collection

Data will be collected over an 18-month period, during regular medical visits to the transplant service and directly entered into the RedCap database by a trained professional. Scheduled patients are randomly selected using routine computerized method. Eligible patients, randomly selected by a list generated with the blockrand package for R language, are invited to participate and to sign the informed consent. Then, the BAASIS interview [28, 43] and the structured questionnaire are applied. The collateral report is completed by the physician/nurse on the same day. Blood levels of immunosuppressive drugs and other clinical variables are extracted from the medical records.

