**Methods/Design:**

This is an observational, cross-sectional, multicentre study that includes 20 Brazilian KT centres. A stratified sampling approach is used, based on strata, with the following characteristics considered: geographical region and transplant activity (number of KTs per year). A random sample of patients (proportional to the size of the centre within each stratum) is selected from each centre. The prevalence of different health behaviours is assessed through self-report. The assessment of multilevel correlates of non-adherence is guided by the ecological model that considers factors at the level of the patient, health-care professional, and transplant centre, using established instruments or instruments developed for this study. Data will be collected over an 18-month period, with information obtained during the regular follow-up visits to the transplant outpatient clinic and directly entered into the Research Electronic Data Capture (RedCap) system. Data entry is performed by a trained professional who is part of the transplant team. The data collection began in December 2015.

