Our study has certain limitations. First, although the 20 centres included in the study were representative of different kinds of centres and regions of Brazil, these centres were selected and recruited by convenience, which allowed our study to be economically feasible and to achieve a potential low dropout rate. Although centres were selected by convenience, patients were randomly selected. Second, due to limited resources, it was not possible to evaluate non-adherence to immunosuppressants using electronic monitoring. We opted to apply a combination of diagnostic methods [27], (i.e. patient self-report, collateral report from nurse/physician, and immunosuppressive blood levels) which has previously been shown to provide the highest sensitivity compared to electronic monitoring [29]. Our evaluation of the CIM model is limited but, to our knowledge, this will be the first time that this model is being evaluated within the context of KT. Finally, as a cross-sectional study, causality between identified factors and non-adherence to post-KT treatment cannot be inferred.

In conclusion, the ADHERE Brazil study is a cross-sectional study evaluating various aspects of non-adherence behaviour to the treatment regimen, and multi-level correlates to immunosuppressive medication non-adherence in 1130 patients across 20 KT centres. Data from this study will provide evidence to people involved in treating KT patients (health care professionals, health care policy makers) regarding the level (patient, health care professional, and health care system and policies) at which further interventions should be implemented to improve adherence to the post-KT treatment and, consequently, the long-term outcomes.

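### The any-positive non-adherence outcome includes a report by the centre's own staff, so centre comparisons and practice-pattern associations may partly reflect how often staff detect non-adherence

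*Protocol article*

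**What the plan says.** **Outcome.** Under Behavioural factors, adherence to immunosuppressants is measured by BAASIS, blood assay and a collateral report by health care workers. The combination rule is: "Overall non-adherence to immunosuppressants will be defined by a positive finding on any one of the three assessment methods". The same section adds: "In addition to the evaluation provided by each individual method, a composite adherence score is calculated".

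**Who rates.** Patient data collection states: "The collateral report is completed by the physician/nurse on the same day". The limitations paragraph of the Discussion lists the methods again as "patient self-report, collateral report from nurse/physician, and immunosuppressive blood levels".

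**What is compared.** At the organisation (meso) level, on chronic illness management, the plan states: "we include questions on patient-centred care, continuity and coordination of care, information and communication technology". These data come from a questionnaire answered by a nurse or physician of the centre. Under Aim 2 of the statistical analysis plan, the binary non-adherence indicator is related to the multilevel correlates by GEE, and the sampling section treats centres as clusters. Aim 3 benchmarks the centres, and each centre is to receive a report comparing it with the others.

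**What is claimed.** The Discussion says that the measurement method will "allow us to conduct reliable comparisons between centres, regions, and clinical practice patterns". It also suggests that practice patterns linked to adherence may be the study's most valuable contribution and could be adopted quickly. The limitations cover the convenience choice of centres, the lack of electronic monitoring, the limited evaluation of chronic illness management and the cross-sectional design. They do not mention detection that differs by centre.

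**The concern.** With an any-positive rule, a further method can only add positives. The third method here is completed by staff who differ from centre to centre. Some of the exposures (continuity, coordination, patient-centred care) describe how closely those staff work with their patients. If such a practice changes how often staff recognise or suspect non-adherence, the outcome is misclassified differently at different levels of the exposure.

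A larger sample does not remove that bias. GEE clustering does not remove it either: it deals with correlation within centres when standard errors are computed, and leaves the recorded outcome as it is. At stake are the organisation-level part of Aim 2 and the medication-adherence part of the benchmark. If a practice raises detection, a real benefit could be hidden or could appear as harm.

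**Working it through.** The plan gives no sensitivity or specificity for any method, so it has no figure of its own to reproduce on this point. All accuracies and true prevalences below are assumptions, chosen only to show the order of magnitude.

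**Formulas.** Let p be the true prevalence, s0 and c0 the sensitivity and specificity of BAASIS-or-assay, and s and c those of the staff report. With errors independent given true status:

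- composite prevalence = p[1 − (1 − s0)(1 − s)] + (1 − p)(1 − c0·c)
- two-method prevalence = p·s0 + (1 − p)(1 − c0)

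**Illustration A: the same true prevalence, p = 0.40, in both centres.** BAASIS is 0.50/0.90 and assay 0.40/0.90. Then s0 = 1 − 0.50 × 0.60 = 0.70 and c0 = 0.90 × 0.90 = 0.81. The two-method figure is 0.40 × 0.70 + 0.60 × 0.19 = 39.4% in both centres.

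| Staff report (sensitivity/specificity) | Composite | Prevalence ratio |
|---|---|---|
| 0.20/0.90 | 0.40 × 0.76 + 0.60 × 0.271 = 46.7% | reference |
| 0.60/0.90 | 0.40 × 0.88 + 0.60 × 0.271 = 51.5% | 1.10 |
| 0.20/0.95 | 0.40 × 0.76 + 0.60 × 0.2305 = 44.2% | reference |
| 0.60/0.85 | 0.40 × 0.88 + 0.60 × 0.3115 = 53.9% | 1.22 |

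With equal staff specificity the gap is p(1 − s0)(difference in s) = 0.40 × 0.30 × 0.40 = 4.8 percentage points.

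**Illustration B: other inputs.** Staff specificity is 0.95 and staff sensitivity rises from 0.2 to 0.6.

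| s0, c0 | Composite at p = 0.50 | Ratio at p = 0.50 | Ratio at p = 0.30 |
|---|---|---|---|
| 0.6, 0.9 | 41.2% to 49.2% | 1.19 | 1.16 |
| 0.7, 0.85 | 47.6% to 53.6% | 1.13 | 1.10 |
| 0.8, 0.8 | 54.0% to 58.0% | 1.07 | 1.06 |

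A deliberately wide contrast (staff 0.1/1.0 against 0.7/0.9) gives ratios from 1.20 to 1.52. The verdict does not rest on it.

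**Dependence on overlap.** The composite exceeds the two-method figure exactly by the share of patients positive on the staff report alone. In Illustration A with equal specificity, suppose the true cases that staff detect are all among those already found by BAASIS or assay. Composite sensitivity is then 0.70 in both centres, and the 4.8-point gap falls to zero.

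**Can the sign change?** Keep Illustration A with equal specificity, but let the centre with the more sensitive staff truly have 36% against 40% (true ratio 0.90).

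- Composite: 0.36 × 0.88 + 0.64 × 0.271 = 49.0% against 46.7%, ratio 1.05.
- BAASIS plus assay: 0.36 × 0.70 + 0.64 × 0.19 = 37.4% against 39.4%, ratio 0.95.

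Under these assumptions a modest true benefit reverses with the composite and keeps its direction without the staff report.

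**The case against.** **Single-method results are already planned.** This stands in part. BAASIS-only and assay-only results leave out the staff report, so it would be wrong to infer that the composite is the only outcome. However, nothing in the text ties the Aim 2 models or the benchmark to those results, and no rule says what happens if they disagree with the composite.

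**The report may not be free opinion.** The instruments are described in Additional file 1, which is not at hand, so the report could be a structured item with fixed criteria. This stands, and the point does not need it to be opinion. Fixed criteria would narrow the differences between centres, but the raters would still differ.

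**Order of rating.** A reader might infer from Patient data collection that staff rate after seeing the BAASIS answers and blood levels. The text says only that it is the same day. Under an any-positive rule a rater who copies a positive result changes nothing, because that patient already counts. No conclusion is drawn from rating order.

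**Size and direction are assumed.** This stands. Staff who know their patients well might trust them too readily and report less. A reader might infer that centres with good continuity will look worse. The documents show only that this is possible.

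**Dropping the staff report has a price.** The methods were combined to gain sensitivity, which is the stated rationale in the Background and the Discussion. The two-method outcome may also vary by centre: BAASIS is applied by interview, and the abstract says "Data entry is performed by a trained professional who is part of the transplant team". The equal two-method figures in Illustration A follow from setting BAASIS and assay accuracy equal across centres. This is why the fix asks for both outcomes and does not replace the composite.

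**Scope.** Smoking, alcohol, physical activity and appointment keeping are assessed by separate questions, so the benchmark is affected only in its medication-adherence part.

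**Conclusion.** The point holds as a design weakness in the centre-level use of the composite. Each link is in the protocol article: a component completed by centre staff, an any-positive rule, practice patterns as correlates, and a comparison of centres. That these practices influence detection is plausible but is not shown in the documents. The claim of reliable comparisons between centres and practice patterns is therefore stronger than the measurement supports.

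Under the moderate assumed contrasts, with independent errors and no true difference, the spurious prevalence ratio is about 1.1 to 1.2 (lowest value 1.06). It approaches 1 as staff detections overlap with BAASIS or assay positives. The upper figure of 1.22 also requires staff specificity to be worse at the centre with higher staff sensitivity. The documents do not support saying that the bias is present, how large it is or which way it runs. The national prevalence under the stated composite definition is not challenged here.

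**What to change.** Add to the analysis plan for Aims 2 and 3:

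1. Organisation-level models and the medication-adherence part of the benchmark are reported with two outcomes: the three-method composite, and BAASIS plus blood assay without the collateral report.
2. A practice-pattern association is concluded only if it is consistent across both. Since the plan avoids significance thresholds, consistency can be judged on direction, size and 95% confidence interval.
3. Centre-dependent detection is named as a limitation, and the Discussion's statement about reliable comparisons is softened to match.

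Keep the three-method composite for the national prevalence.

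The cost is analysis work and wording. The two-method outcome uses data that the study already collects, so the change does not depend on data collection, which was due to end in June 2017. The downside is that the two-method outcome is less sensitive. Agreement between the two outcomes does not rule out centre differences in the BAASIS interview itself.
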